### Eligibility

Consistent with the partnering requirements of the funding opportunity announcement, we will be targeting all FDOH-contracted or direct service agencies (N=42) across all 7 EHE counties of Florida that meet the following eligibility criteria: (1) provide HIV CTR services and (2) have tested at least 24 young sexual minority men in 2021. FDOH has agreed to the participation of these 42 agencies. Given that a few agencies may cease operations or may be either unable or unwilling to adopt the implementation strategies, we conservatively estimate that we will need 36 agencies that have tested at least 24 young sexual minority men within each cluster.

### Hiring and Training of MSs

We will hire and train 4 to 6 MSs per region (north Florida, central Florida, and south Florida) to conduct QM assessments throughout the study period. We will use both active (eg, directly approaching young sexual minority men) and passive strategies (eg, posting advertisements on social media) to identify HIV-negative young sexual minority men (aged 18-29 years) who are interested in serving as MSs. We will also promote the opportunity via advertisements on various platforms. These platforms include lesbian, gay, bisexual, and transgender (LGBT) listservs; college listservs; HIV and AIDS community-based organizations; and local coffee shops and bars. In addition, we will use social media platforms and dating apps such as Jack’d (Perry Street Software), Facebook (Meta Software), Instagram (Meta Software), LinkedIn (Microsoft), and Idealist (Free Software Foundation).

MSs will participate in a training session that will follow the procedures we used in our previous studies [11]. Specifically, MSs will receive a structured 2-hour training session on the fundamentals of HIV or STI transmission, the guidelines and protocols surrounding HIV or STI testing and PrEP eligibility, and state-specific HIV guidelines and policies. MSs will also be trained to complete the assessment tool to optimize standardized data collection across agencies.

We will underscore the importance of being well versed in their rights and procedures, and increase skills on how to respond to worst-case scenarios (eg, how to turn down any unwanted procedures), were they ever to occur. MSs will be instructed to be honest about their sexual behaviors during their visits. For an HIV-positive test result, MSs will alert the study staff who will provide referrals for care, if needed.

MSs will be randomly assigned to each study site to avoid selection bias. The team will create a calendar for MSs to know their schedule of clinic visits. MSs will be instructed to report that they do not have income or health insurance and do not possess any proof of identification. By doing so, we will ascertain whether these are potential barriers to testing at a given location and document the lowest possible fees that may be charged to a young sexual minority man.

### MS Site Assessment Measure

MSs will complete a web-based agency checklist and qualitative debrief with study staff to summarize their impressions of the following: (1) how they felt about the agency, (2) interaction with the counselors and testing providers, (3) anything notable that occurred in the course of the visit (be it positive or negative), and (4) any other information deemed pertinent to the experience. Assessment training will include a discussion on the definition, understanding, and measurement of each mystery shopping domain (Table 1). The 11 mystery shopping domains include 9 that were previously used to assess HIV-testing sites in our previous studies along with 2 new domains focused on cultural humility and MI based on validated scales [47,48].

**Table 1 table1:** Mystery shopping site assessment domains.

Domains	Items assessed	Interpersonal or environmental factor
Medical form inclusivity	Clinic used LGBT^a^-inclusive language on forms	Environmental
Clinic environment	Friendliness, sensitivity, use of affirming language by staff, lack of judgment, and comfort of waiting room	Interpersonal and environmental
Privacy and confidentiality	Patient info kept confidential by office staff and testing provider, privacy in waiting room, and confidentiality explained	Interpersonal and environmental
PrEP^b^ information and dialogue	Presence of PrEP information and whether testing provider shared info about PrEP as a prevention strategy	Interpersonal and environmental
Relationship context	Testing provider asked about sexual orientation, relationship status, sexual activity, and experiences with intimate partner violence	Interpersonal and environmental
RRC^c^	Testing provider explored motivation for testing, offered to help set safer sex goals and action steps, and presented risk reduction options	Interpersonal
Safer sex education	Testing provider helped me to identify condom and lube that work for me and made sure I know how to use them, and discussed PrEP as prevention strategy	Interpersonal and environmental
Testing provider knowledge	Testing provider was knowledgeable about HIV and STIs^d^ and LGBT health issues	Interpersonal and environmental
Testing provider interactions	Testing provider made me feel comfortable, was not judgmental about my sexual activity or partners, did not pressure me to adopt risk reduction options	Interpersonal
Cultural humility	Testing provider was knowledgeable, understanding, or curious about my cultural background, or made assumptions about my cultural experiences	Interpersonal
Client-centeredness	Clinic staff took a collaborative stance when discussing making healthy changes, supported my autonomy, helped me recognize need for change and feel confident in my ability without acting as an authority	Interpersonal

^a^LGBT: lesbian, gay, bisexual, and transgender.

^b^PrEP: pre-exposure prophylaxis.

^c^RRC: risk reduction counseling.

^d^STI: sexually transmitted infection.

### YACHT Implementation Package Specification

#### Overview

During the exploration phase, we will present at state-wide meetings and conferences to inform agencies state-wide about the initiative in collaboration with FDOH. Every quarter, each study site will receive 2 MS visits. We will use time-space sampling to ensure that varying days (weekdays vs weekends, when applicable) and times (eg, morning vs afternoon or evening) are selected for visits, thereby maximizing the chance of meeting different counselors at each agency. The exploration phase will end with virtual meetings of individual agencies with regional facilitators to orient HIV-testing directors to the program, address any initial concerns, and increase engagement with the planned implementation strategies. These meetings will aim to create an engaging, interactive environment to probe knowledge and utility of MSs for HIV-testing programs. Regional facilitators will describe the MS assessment and approaches using TMI and TA, ending the session with an overview of the study and scheduling an in-person visit for the preparation phase.

The preparation phase will occur 2 months before the implementation phase and will consist of an in-person meeting with the executive director and the leads of testing and prevention services. We will provide personalized feedback using the MS assessment findings that address environmental and interpersonal factors. We will elicit their views regarding the findings, focusing on the aspects they would like to improve. We will also suggest strategies for change and assist them with planning an intervention appropriate for their agency. To address environmental factors, we will lead agency directors in a problem-solving exercise to brainstorm ideas and develop a plan to address the components they select. To address the interpersonal factors, we will discuss how TMI may be used to improve testing provider–client interactions and discuss challenges and opportunities for improving CTR services. In collaboration with the agency, we will compile a list of staff to engage in the intervention. Consequently, the YACHT program will be adapted to each agency’s needs and culture.

The implementation phase (12 months) will consist of quarterly 1-hour QM meetings in which we will review data regarding adherence to the implementation plan (eg, staff attendance at TMI training) as well as the most recent MS assessments, iteratively revising the implementation plan as needed. TA tailored to the areas of need identified during the preparation phase will be offered throughout the implementation period. We will use a facilitated problem-solving approach consisting of the following 4 steps: (1) define and analyze the problem, (2) generate new ideas, (3) analyze potential solutions, and (4) implement and evaluate the plan. In addition, to build testing provider’s interpersonal counseling skills, we will offer TMI options as follows:

#### Initial TMI Workshop

This workshop is theoretically grounded in behavior modification and behavioral skills training developed by Bandura [49] and Miltenberger [50] as well as research in education on cooperative learning environments [51,52]. Originally designed as a 2-day in-person training, we will deliver TMI workshop virtually via structured web-based modules followed by two 3-hour interactive modules on Zoom with cooperative learning activities, video examples, and behavioral skills acquisition steps (modeling, verbal and behavioral rehearsal, and feedback). We have further adapted these TMI modules to ensure delivery from a foundation of cultural humility [53] and antiracism [54], emphasizing how learners engage in a lifelong process of self-reflection and self-critique, challenge power dynamics, commit to understanding and respecting different points of view, and engage with others authentically and from a place of learning. Discussion sessions will focus on moving from not racist to antiracist while concepts of cultural humility with video examples will be interwoven throughout training. Participants will practice how to use TMI skills to demonstrate cultural humility in language with video demonstrations.

#### Coded Standard Patient Interactions With Automated Feedback

After participating in the workshop, testing providers will complete a 15- to 20-minute long standard patient interaction by phone. TMI coaches will code the interactions with the Motivational Interviewing Coach Rating Scale (MI-CRS) [47,55]. The MI-CRS consists of 12 items rated on a 4-point scale (beginner, novice, intermediate, and advanced) representing essential MI components such as a collaborative stance, autonomy support, open questions to elicit motivational language (ie, change talk), reflections of change talk, affirmations, cultural humility, and summaries. Testing providers will receive an autogenerated report based on scores with recommendations for practice activities and links to short videos of skill demonstration, including newly developed cultural humility videos, based on the lowest scoring items. These scores will guide the group coaching (discussed next) and will also be repeated at 6 months to provide further feedback.

#### Group Coaching

Standardized 1-hour virtual coaching sessions (up to 4 per agency) will include a brief interaction to elicit motivation for TMI implementation and then, behavioral skills acquisition based on the lowest ratings received on the most recent MI-CRS and MS assessments. The coaching of each skill will follow the skills acquisition steps of modeling, verbal and behavioral rehearsal, and feedback.

In the sustainment phase, agencies will be randomized to either continue receiving written feedback from the quarterly MS assessments or no additional feedback. Agencies will not have any contact with the TMI coaches during this period; however, agencies may continue to seek TA from FDOH as standard of care.

#### EPIS Fidelity Procedures

In the exploration phase, MSs will complete the site assessments. We will also have site communication logs in which the facilitator for each study site will document contact with sites, including e-mails, phone calls, and meeting notes. In the preparation phase, each site will have a personalized feedback report based on the MS assessments, and we will continue to document contact in the site communication logs. We will also have a checklist of completed steps and of potential facilitators of and barriers to engagement in implementation. Finally, we will develop and document an implementation plan for each site. In the implementation phase, we will document (1) review of new MS data and any agency data regarding testing, (2) review of adherence to implementation plan, (3) provision of TA to overcome barriers and enable facilitators, (4) revision of implementation plan, and (5) development of sustainment plan at the last QM meeting. Furthermore, 1 TMI group coaching session per block will be randomly selected and coded by the study’s principal investigator for content and TMI consistency with the MI-CRS. Finally, agency directors, supervisors, and staff will be interviewed to determine barriers to and facilitators of YACHT fidelity. In the sustainment phase, agencies will be referred to health departments for ongoing TA and another round of interviews will be conducted at the end of the phase with the same staff to identify the barriers to and facilitators of sustaining EBPs.

#### Quantitative Measures and Data Analysis

Data are nested, which will be addressed using mixed-effects regression models. The key feature is that a minimum of 36 (out of 42 recruited) agencies are nested within the 7 counties. We will explore the use of random intercept at the county level. With only 7 counties, our model may run into convergence and estimation issue. In such a situation, we will include appropriate fixed-effects indicators in our model. We will request FDOH data on the number of HIV tests administered in quarterly intervals during all 3 phases (preintervention, intervention, and sustainment).

#### Primary Effectiveness Outcome

The primary outcome is the number of tests completed by young sexual minority men (aged 18-29 years), as reported in aggregate at the agency and county levels. We expect that the YACHT package will improve the number of HIV tests administered to young sexual minority men at each agency. As an exploratory outcome, FDOH has recently begun tracking PrEP uptake. Both the testing and PrEP data are reported in a standardized fashion to FDOH. Data will be aggregated within agencies and will be requested biannually. We have budgeted for staff at FDOH to manage data and deliver it in analyzable format. Data will be managed into quarterly windows to correspond to the data collection intervals in the stepped wedge design.

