## Results

The study was funded on August 4, 2022. A simple randomization scheme was generated using SAS (version 9.4; SAS Institute) to assign agencies to receive feedback versus no feedback during the sustainment phase on April 18, 2023. MS visits were initiated on June 1, 2023. As of June 2024, 194 MS visits have taken place at 42 sites. In addition, 4 sites from the first block and 1 site from the second block have engaged with the study. At baseline assessment, sites exhibited the lowest competencies in relationship context, counseling session, and safer sex education, and the highest competency in the privacy and confidentiality domain.

The exploration phase is projected to last from June 1, 2023, to March 31, 2024 (10 months), for block 1 and until September 30, 2025, for block 7 (28 months), with the other blocks staggered every 3 months. The preparation phase for block 1 started on April 1, 2024, and is projected to take up to 2 months for each block. The implementation phase will last for 1 year and started on June 1, 2024, for block 1 and will begin on December 1, 2025, for block 7, with other blocks staggered every 3 months. Finally, the sustainment phase will start on June 1, 2025, for block 1 and last for 2 years. For block 7, it will start on December 1, 2026, and continue for 6 months. Data collection will be completed by May 31, 2027.

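### As worded, the primary outcome counts the mystery shoppers' own HIV tests, and the rate ratio can be biased in either direction unless they are removed

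*Protocol article*

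**What the plan says.** The Primary Effectiveness Outcome section of the protocol article defines the endpoint: "The primary outcome is the number of tests completed by young sexual minority men (aged 18-29 years), as reported in aggregate". The source is FDOH reporting: "Data will be aggregated within agencies and will be requested biannually". The data are then arranged into quarters. Analytic Strategy names a Poisson or negative binomial mixed model that estimates a ratio, with an agency random effect and adjustment for calendar time and exposure time.

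Hiring and Training of MSs says that recruitment seeks "HIV-negative young sexual minority men (aged 18-29 years) who are interested in serving as MSs". Shoppers are to be honest about their sexual behavior, and to say that they have no income, insurance or identification. The same section provides for a shopper's result: "For an HIV-positive test result, MSs will alert the study staff who will provide referrals for care, if needed".

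The Overview of the implementation package fixes the frequency: "Every quarter, each study site will receive 2 MS visits". Study Design keeps the visits going through implementation. Group Coaching shows that quarterly assessments also continue in sustainment, where only the feedback is randomized.

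Under Eligibility, agencies must "have tested at least 24 young sexual minority men in 2021". Results reports progress: "As of June 2024, 194 MS visits have taken place at 42 sites".

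No section says that shopper tests are excluded, flagged or subtracted. None says outright that they are counted.

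**The concern.** The shoppers match the outcome population in age, sex and sexual orientation, and they present as ordinary clients. An agency that tests one of them would normally report the test with its others. Since FDOH delivers aggregate counts, such tests cannot be identified afterwards without the study's own records.

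Running the visits through all phases does not make them cancel. A constant added to both sides of a ratio shrinks it. If the number added differs between phases, the ratio can move either way. The second case matters because the shoppers' script is meant to reveal obstacles to testing, and the package then feeds the findings back so that agencies can remove them. The study's own measurement could then appear as a gain in community testing.

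**Working it through.** **Inputs from the article**
- Planned visits: 2 per site per quarter. Over June 2023 to May 2027 (16 quarters) at 42 sites, 42 × 2 × 16 = 1,344.
- Smallest eligible agency: 24 men per year, 24/4 = 6 per quarter, taking one test per man.
- Delivered in roughly the first 12 months: 194 of 42 × 2 × 4 = 336 planned (58%), or 194/168 = 1.155 per site-quarter.

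**Assumptions, because the article gives no figure**
- True ratio 1.30.
- Genuine volumes of 6, 12, 25 and 50 tests per quarter.
- One reported test per shopper visit, varied below.

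**Formula.** With λ genuine tests per quarter, true ratio θ, and m0 and m1 shopper tests per quarter before and after crossover:

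observed ratio = (λθ + m1) / (λ + m0)

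**Case 1: equal shopper tests before and after (m0 = m1), θ = 1.30**

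| λ | Shopper share of baseline count, m = 2 | Observed ratio, m = 2 | Log effect lost, m = 2 | Observed ratio, m = 1.155 |
|---|---|---|---|---|
| 6 | 2/8 = 25% | 9.8/8 = 1.225 | 23% | 1.252 |
| 12 | 2/14 = 14% | 17.6/14 = 1.257 | 13% | 1.274 |
| 25 | 2/27 = 7% | 34.5/27 = 1.278 | 7% | 1.287 |
| 50 | 2/52 = 4% | 67/52 = 1.288 | 3% | 1.293 |

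The loss is 1 − ln(observed)/ln(1.30); at λ = 6, 1 − ln(1.225)/ln(1.30) = 23%. If only half the visits yield a reported test (m = 1), λ = 6 gives 8.8/7 = 1.257, a 13% loss. Other true ratios at λ = 6 and m = 2: 1.2 becomes 9.2/8 = 1.150, and 1.5 becomes 11/8 = 1.375. A true 1.00 stays at 1.00.

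A Poisson regression on expected counts over the trial's calendar (42 agencies, 7 blocks, starts at months 12 to 30, agency and time effects) gives the same 1.225 at λ = 6 and 1.257 at λ = 12. With shopper tests removed it returns 1.30.

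**Case 2: share of visits ending in a test rises from 50% to 100% at crossover (m0 = 1, m1 = 2)**
- λ = 6: true 1.30 becomes 9.8/7 = 1.40, and true 1.00 becomes 8/7 = 1.14.
- True 1.00 at larger volumes: λ = 12, 14/13 = 1.08; λ = 25, 27/26 = 1.04; λ = 50, 52/51 = 1.02.

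**Case 3: visit completion rises over calendar time.** Going from 1.155 to 2 per quarter gives a raw before/after ratio of 8/7.155 = 1.12 at λ = 6. That is not the bias in the intervention effect. Block 1 crosses over on June 1, 2024, so all blocks are preimplementation throughout year 1, and the model adjusts for time. Fitting that rise with a true ratio of 1.00 and every agency at λ = 6 gives 0.98 to 1.02 with linear time, 0.997 to 1.005 with quadratic time and 1.000 with categorical time.

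**The case against.** The strongest reply is that the inclusion is inferred from silence in a condensed article. A full protocol or analysis plan could subtract these tests, and the team knows its own visit dates. Nor need each visit end in a test: shoppers arrive without identification or insurance so that barriers can be detected, and they are trained to refuse unwanted procedures. The sentence on positive results shows that some are tested, not that all are. How FDOH codes them is unknown.

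This stands as a limit on size. It does not remove the point, because the article does fix what the primary endpoint counts, and that definition takes in the shoppers' tests.

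A reader might infer four stronger claims that the documents do not support:
- **Every visit adds one reported test.** This is only an assumption.
- **The bias is always toward 1.** That requires equal shopper tests before and after crossover.
- **The year-1 shortfall in visits creates a false 12% rise.** Time adjustment reduces it to about 2% or less. Principal Findings mentions sites opting out of visits, but Results reports visits at 42 sites, and stable differences between agencies are largely absorbed by the agency effect.
- **The trial as a whole loses 23% of its log effect.** That figure belongs to agencies at the eligibility minimum, and larger agencies carry more information in a count model.

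**Conclusion.** The point holds in limited form. The primary outcome, as written, includes tests that the study itself generates, and no exclusion is stated. With equal shopper tests before and after crossover, a true 1.30 is seen as 1.225 to 1.288 across 6 to 50 genuine tests per quarter: material near the eligibility floor, small at high volume, and no false positive under the null. If the intervention raises the share of shopper visits ending in a test, the bias can run away from 1, up to about 1.14 for a true null in the floor-size example. These figures assume that shopper tests reach FDOH coded to this group; the Case 1 table and the upper end of Case 2 also assume one test per visit. Drift in visit completion over calendar time is not a main concern. The trial-wide bias cannot be computed without agency volumes and the share of visits that ended in a test.

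**What to change.** Define the primary count as the FDOH agency-quarter count minus the shopper visits in that agency and quarter that ended in an HIV test. Take these from the study's visit schedule and post-visit checklist. If the checklist does not already record whether a test was done, add that item now; data collection runs to May 2027. Report the unadjusted count as a sensitivity analysis.

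The cost is a sentence in the outcome definition, possibly one checklist item, and a merge by agency and quarter.

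The downside is over-subtraction where FDOH did not code a shopper's test to this group. At λ = 6 with a true 1.30 and 2 tests subtracted, 90% coding gives (7.8 − 0.2)/(6 − 0.2) = 1.31, which is slight. The extreme of no coding gives 5.8/4 = 1.45, while the unadjusted ratio would then be correct at 1.30. With stable shopper tests, the net and unadjusted ratios therefore bound the true value, which is why both should be reported.
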